## Abstract

**Background:**

Health problems in neonates with gestational age (GA) ≥ 32 weeks remain a major medical concern. Respiratory distress (RD) is one of the common reasons for admission of neonates with GA ≥ 32 weeks. Noninvasive ventilation (NIV) represents a crucial approach to treat RD, and currently, the most used NIV modes in neonatal intensive care unit include high-flow nasal cannula (HFNC), continuous positive airway pressure (CPAP), and nasal intermittent positive pressure ventilation. Although extensive evidence supports the use of NIPPV in neonates with a GA < 32 weeks, limited data exist regarding its effectiveness in neonates with GA ≥ 32 weeks. Therefore, the aim of this study is to compare the clinical efficacy of HFNC, CPAP, and NIPPV as primary NIV in neonates with GA ≥ 32 weeks who experience RD.

**Methods:**

This trial is designed as an assessor-blinded, three-arm, multi-center, parallel, randomized controlled trial, conducted in neonates ≥ 32 weeks’ GA requiring primary NIV in the first 24 h of life. The neonates will be randomly assigned to one of three groups: HFNC, CPAP or NIPPV group. The effectiveness, safety and comfort of NIV will be evaluated. The primary outcome is the occurrence of treatment failure within 72 h after enrollment. Secondary outcomes include death before discharge, surfactant treatment within 72 h after randomization, duration of both noninvasive and invasive mechanical ventilation, duration of oxygen therapy, bronchopulmonary dysplasia, time to achieve full enteral nutrition, necrotizing enterocolitis, duration of admission, cost of admission, air leak syndrome, nasal trauma, and comfort score.

**Discussion:**

Currently, there is a paucity of data regarding the utilization of NIPPV in neonates with GA ≥ 32 weeks. This study will provide clinical evidence for the development of respiratory treatment strategies in neonates at GA ≥ 32 weeks with RD, with the aim of minimizing the incidence of tracheal intubation and reducing the complications associated with NIV.

**Trial registration:**

Chinese Clinical Trial Registry: ChiCTR2300069192. Registered on March 9, 2023, https://www.chictr.org.cn/showproj.html?proj=171491.

## Introduction

### Background and rationale {6a}

Neonates with gestational age (GA) ≥ 32 weeks (including mid-term preterm infants (32–33^+5^ weeks), late preterm infants (34–36^+6^ weeks), and term infants (> 37 weeks)), constitute a significant proportion of births [1, 2]. Data collected from 107 countries revealed that moderate and late preterm infants, as well as term infants, accounted for 98.4% of all neonatal births [2]. The health concerns associated with these infants remain a major medical focus. Among these infants with GA ≥ 32 weeks, respiratory distress (RD) is a common cause for hospitalization [3–5]. RD is defined as the presence of at least two clinical symptoms for a minimum duration of 15 min, which may include tachypnea (respiratory rate > 60/min), subcostal and/or intercostal retractions, expiratory grunting, nasal flaring, and central cyanosis in room air [6]. A prospective study conducted in Switzerland reported that hospitalized neonates with GA ≥ 32 weeks accounted for 85.4% of all neonates with RD [7]. In the neonatal intensive care unit (NICU), RD led to hospitalization for 28.8% of late preterm infants and 15.6% of term infants [5].

Noninvasive ventilation (NIV) plays a crucial role in the treatment of RD, offering effective relief and reducing the occurrence of respiratory failure, tracheal intubation, and invasive mechanical ventilation (IMV) [8, 9]. Currently, the three most used NIV modes in the NICU are high-flow nasal cannula (HFNC), continuous positive airway pressure (CPAP), and nasal intermittent positive pressure ventilation [10–14]. CPAP, being the most widely employed NIV mode, has demonstrated its efficacy in enhancing oxygenation and increasing the success of extubation in earlier clinical trials [10–12, 15]. It is considered an effective choice for primary respiratory support for preterm infants, significantly reducing the need for IMV [16, 17]. HFNC, favored by nursing staff for its ease of use and ability to minimize nasal trauma, has gained extensive utilization in neonates [18–20]. While NIPPV, a relatively newer NIV mode, has been studied in very preterm infants, evidence regarding its effectiveness in neonates with GA ≥ 32 weeks remains limited.

Many studies have shown that NIPPV is superior to CPAP in reducing tracheal intubation and apnea in neonates with GA < 32 weeks [21–24]. When compared to CPAP, NIPPV exhibits significant reductions in respiratory failure, apnea, tracheal intubation, and extubation failure among preterm infants born before 37 weeks [25–27]. However, there is a relative scarcity of evidence regarding the comparison between NIPPV and CPAP specifically in neonates with GA ≥ 32 weeks. Further studies in this population are warranted to provide a clearer understanding of the effectiveness of NIPPV in comparison to CPAP.

There is limited evidence comparing the effectiveness of NIPPV and HFNC in neonates with GA ≥ 32 weeks. Two randomized controlled studies [28, 29] have been conducted, one including neonates with GA less than 35 weeks and the other including neonates with GA less than 34 weeks. These studies reported no significant difference between HFNC and NIPPV in preventing treatment failure. However, it is important to note that the sample sizes of these two studies were relatively small, suggesting the need for larger-scale research to further investigate and validate these findings.

Several studies have provided evidence supporting the superior outcomes of NIPPV over CPAP in terms of reduced treatment failure rates and tracheal intubation incidents [21–24]. However, due to the higher cost and greater technical complexity of NIPPV equipment, many clinical centers prefer to use CPAP as the primary respiratory support for neonates [30]. It has been reported that neonates with higher respiratory scores [31] have a higher increase in the need for respiratory support within 24 h [32]. In the case of neonates with GA ≥ 32 weeks, some individuals present with severe RD, and early implementation of more advanced NIV methods may potentially prevent the exacerbation of their condition, consequently reducing the incidence of tracheal intubation and mechanical ventilation. Therefore, our proposed research plan includes a subgroup analysis based on the severity of RD, aiming to investigate the effectiveness of NIPPV, CPAP, and HFNC in preventing treatment failure among neonates with varying degrees of RD severity.

Therefore, we will conduct a multicenter randomized controlled trial to investigate the effectiveness and safety of NIPPV in neonates with GA ≥ 32 weeks with RD and select the best primary NIV mode for these infants. We will compare the clinical effectiveness and safety in preventing treatment failure of HFNC, CPAP, and NIPPV as primary respiratory support in neonates with GA ≥ 32 weeks with RD through this study.

### Objectives {7}

The objective of this study is to compare the clinical effectiveness of HFNC, CPAP, and NIPPV as primary respiratory support in neonates with RD who are ≥ 32 weeks GA in reducing the need for IMV. We hypothesize that NIPPV is more effective than CPAP and HFNC in preventing treatment failure in neonates ≥ 32 weeks GA.

### Trial design {8}

This trial is designed as a three-arm, multicenter, parallel, randomized controlled trial with assessor blinding, with random allocation in a 1:1:1 ratio. It is a superiority clinical trial.

## Methods: participants, interventions, and outcomes

### Study setting {9}

This trial will be conducted at three centers: West China Second University Hospital, Sichuan University, Jinjiang Campus; West China Second University Hospital, Sichuan University, Ren Nan Campus; and Sichuan Provincial Children’s Hospital, which are tertiary hospitals equipped with ventilators capable of providing HFNC, CPAP, and NIPPV. Those participating centers have experienced medical staff who possess the necessary skills and expertise in treating and caring for infants receiving NIV. To ensure efficient data collection and management, the research data from each center will be transmitted and shared using electronic documents. This approach facilitates streamlined data exchange and minimizes the risk of data loss or errors during the research process. Standardized protocols for data collection, including relevant clinical parameters and outcomes, will be established to maintain consistency across all participating centers.

### Eligibility criteria {10}

#### Inclusion criteria

The inclusion criteria for infants participating in the trial are as follows:They are born at ≥ 32 weeks GA; andTheir birth weight ≥ 1200 g, andRD occurred within 24 h after birth (RD is defined as the presence of any two or more of the following symptoms: tachypnea, chest retraction, or grunting) [33].

#### Exclusion criteria

Infants will be excluded from the trial if they meet any of the following criteria:They have a history of prior trachea intubation or require trachea intubation as determined by the attending pediatrician; orThey have major congenital anomalies or chromosomal abnormalities; orThey are suspected congenital lung diseases, malformations, or pulmonary hypoplasia; orThey have neuromuscular disorders; orThey have known air leak syndrome; orTheir parents don’t provide agreement or refuse to allow the infants before randomization.

### Who will take informed consent? {26a}

Guardian’s consent must be obtained before enrolling if the infant is eligible after admission. Full verbal and written informed consent must be included. The informed consent will be obtained by personnel with good clinical practice (GCP) qualifications.

### Additional consent provisions for collection and use of participant data and biological specimens {26b}

This study does not involve the collection of biological samples.

## Interventions

### Explanation for the choice of comparators {6b}

Given the established safety profiles and widespread usage of CPAP, NIPPV, and HFNC in neonatal care [16, 17, 25, 34], it is reasonable to consider these respiratory support modes as both control and intervention groups in this study. We plan to conduct paired comparisons; each group will serve as both a control and an intervention group.

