### Sample size {14}

As this study aims to compare the effectiveness and safety of NIPPV, CPAP, and HFNC in infants with GA ≥ 32 weeks, we plan to conduct paired comparisons. Since no studies with identical content to this study have been conducted in the past, we will refer to the following studies for sample size calculation. A trial comparing CPAP and BiPAP including neonates of GA ≥ 34 weeks with transient tachypnea of the newborn, showed that BiPAP had lower treatment failure (CPAP: 20%, BiPAP: 7.9%, P: 0.03) [42]. In addition, a prospective randomised controlled trial comparing CPAP and HFNC in infants with GA ≥ 31 weeks showed higher treatment failure in the HFNC group (HFNC: 20.5%, CPAP: 10.2%, CI: 10.3) [34]. Therefore, we can calculate the sample size of this trial based on the data from the study [34], in which we will use the treatment failure of HFNC and CPAP as primary respiratory support in neonates as a reference. Considering the trial involving multiple comparisons, using an alpha error rate of 0.0167 and a power of 0.8, at least 252 infants should be enrolled in each arm calculated by PASS15.0.5 software, so the total sample size is 756. Considering 5% loss, the sample size would be no less than 795.

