## Statistical methods

### Statistical methods for primary and secondary outcomes {20a}

Statistical analysis will be performed on the basis of intention-to-treat analysis, according to the Consort reporting guidelines. The normality of continuous outcomes will be tested by Kolmogorov–Smirnov test. Mean difference with 95% confidence interval (CI) will be calculated for normally distributed outcomes and median difference with P25-P75 for non-normally distributed continuous outcomes. Continuous outcomes will be compared by the appropriate parametric (one- way ANOVA) or non-parametric (Mann–Whitney U) test, followed by post hoc test if needed. Dichotomous outcomes will be compared by Chi-square test. Multivariate regression analyses will also be conducted for selected outcomes, if required, and in that case, logistic regression, linear regression, or Cox regression analyses will be performed based on the type and distribution of variables. Specifically, if a baseline characteristic of the enrolled population shows a significant difference (*p* < 0.2) between the two groups in the univariate analysis, the results will be adjusted for that variable. To control for the error of multiple comparisons, the *P*-value of multiple comparisons will be corrected by Bonferroni method. All tests will be two-tailed, and *P* < 0.0167 will be considered significant.

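### The flat 0.0167 Bonferroni rule for the three pairwise tests is valid but needlessly weak: with three arms a step-down rule holds the same 0.05 family-wise error with more power

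*Protocol article*

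**What the plan says.** - **Hypothesis.** Objectives {7}: "We hypothesize that NIPPV is more effective than CPAP and HFNC in preventing treatment failure in neonates ≥ 32 weeks GA". Trial design {8} adds "It is a superiority clinical trial", "with random allocation in a 1:1:1 ratio".
- **Comparisons.** Explanation for the choice of comparators {6b}: "We plan to conduct paired comparisons; each group will serve as both a control and an intervention group". Sample size {14} repeats the plan for paired comparisons. The background section ends with the aim to "select the best primary NIV mode for these infants".
- **Multiplicity.** Statistical methods {20a}: "To control for the error of multiple comparisons, the *P*-value of multiple comparisons will be corrected by Bonferroni method". Tests are two-tailed with significance at P < 0.0167, and the missing-data section {20c} repeats that threshold.
- **Sizing.** Sample size {14}: "using an alpha error rate of 0.0167 and a power of 0.8, at least 252 infants should be enrolled in each arm". The rates used are HFNC 20.5% and CPAP 10.2%. A cited trial with CPAP 20% and BiPAP 7.9% is mentioned but does not enter the calculation, and no NIPPV rate is assumed.

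**The concern.** A single-step Bonferroni rule tests every pair at 0.05/3, however strong the evidence from the other pairs. That protects against three true null hypotheses at once, even after the data have ruled that situation out. With three arms this matters more than usual, because once one pair differs, at most one of the other two pairs can still be equal. Testing those at 0.0167 buys no error control that the trial needs.

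The hypothesis requires two significant contrasts, so the cost falls on the claim that the investigators most want to make. NIPPV v CPAP is the contrast most exposed on the trial's own CPAP rate. A true advantage of NIPPV over both comparators could then be missed because of the testing rule alone.

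**Working it through.** **1. The plan's own figure.** With unpooled variance and two-sided alpha 0.0167:

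n = (z₁₋α/₂ + z₁₋β)² × [p₁(1−p₁) + p₂(1−p₂)] / (p₁−p₂)²

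= (2.393 + 0.842)² × (0.205×0.795 + 0.102×0.898) / 0.103² = 251.1, rounded up to 252.

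The stated 252 per arm reproduces (the pooled formula gives 255). The planned pairwise alpha is therefore two-sided 0.0167.

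**2. Why the step-down rule is valid.** Test all three arms by chi-square at 0.05. Only if that is significant, test each pair at 0.05. The possible truths are:
- All arms equal: an error requires the global test to reject, which has probability 0.05.
- Exactly one pair equal: there is one true null, tested at 0.05.
- Exactly two pairs equal: impossible, because the third pair would then be equal too.
- No pair equal: no false rejection is possible.

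Simulation at 252 per arm agrees. With 15% failure in every arm, the chance of any rejection is 0.044 under Bonferroni and 0.050 under step-down. At 20.5/10.2/10.2%, where only NIPPV = CPAP is true, the false rejection rate under step-down is 0.049.

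**3. One contrast by formula.** NIPPV v CPAP at 4.0% v 10.2%. The 4.0% is the cited BiPAP/CPAP ratio applied to the trial's CPAP rate: 10.2% × 7.9/20 = 4.03%.

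Power = Φ{[|p₁−p₂|√n − z√(2p̄(1−p̄))] / √[p₁(1−p₁)+p₂(1−p₂)]}

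- At 0.0167: (0.062×15.875 − 2.393×0.3632)/0.3606 = 0.32, so power is 62.5%.
- At 0.05: (0.062×15.875 − 1.960×0.3632)/0.3606 = 0.755, so power is 77.5%.

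**4. Joint power by simulation.** Pooled two-proportion z-tests on shared arms, 252 per arm, at least 200,000 trials per scenario. Split means that NIPPV is significant against only one comparator at 0.0167.

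| HFNC/CPAP/NIPPV failure, % | Both shown, flat 0.0167 | Both shown, step-down | Split, flat 0.0167 |
|---|---|---|---|
| 20.5/10.2/4.0 | 64% | 79% | 36% |
| 20.5/10.2/5.0 | 43% | 61% | 57% |
| 20.5/20.5/10.2 | 69% | 83% | 23% |
| 20.5/20/7.9 | 92% | 97% | 7% |
| 20.5/10.2/7.9 | 6% | 14% | 90% |

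The gain is 5 to 18 percentage points. In the last row NIPPV v CPAP has only 6.8% power at 0.0167 and 14.4% at 0.05. The small assumed difference is the limit there, not the testing rule.

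**5. A limit of the chi-square gate.** A pair just at the Bonferroni threshold has z² = 2.393² = 5.73, below the 5.99 that the two-degree-of-freedom global test needs. If the third arm lies midway, Bonferroni can therefore reject where the gate does not. This is rare. The Shaffer step-down avoids it: the smallest of the three P-values at 0.0167 and, if that is significant, the other two at 0.05. Holm avoids it too (0.0167, 0.025, 0.05) but gains less power.

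**The case against.** **Bonferroni is prespecified, valid and matches the sizing alpha, so replacing it is preference.** Its validity stands and no error-rate fault is alleged. But a rule with the same family-wise guarantee, the same three testable pairs, no extra infants and up to 18 points more power on the stated hypothesis is better by a criterion that the protocol itself accepts.

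**Equal treatment of the pairs suits the objective.** This also stands. The objective is to compare three modes, and HFNC v CPAP belongs to it. The step-down rule keeps that pair. If the only claim were that NIPPV beats both, each contrast could be tested at 0.05 with no gate, but claims about single pairs would then lose their protection.

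**Changing the threshold after recruitment began on September 1, 2023, with unblinded clinicians, invites doubt.** This is fair, and it governs how the change is made.

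Three stronger readings are tempting and are not supported:
- *That the plan does not name the deciding contrasts.* The hypothesis names both NIPPV contrasts and joins them with "and". An explicit win rule is detail that an article may leave to the full protocol or analysis plan.
- *That a split result gives opposite verdicts.* Each pair carries its own error-controlled conclusion. Reporting NIPPV as better than HFNC but not shown better than CPAP is coherent, and the protocol promises no single overall verdict.
- *That a split is likely.* The 90% figure pairs BiPAP 7.9% from one cited trial with CPAP 10.2% from another. Keeping the first trial's own CPAP rate gives 7%.

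**Conclusion.** The flat 0.0167 threshold is sound but inefficient for the primary outcome. A step-down rule holds the same 0.05 family-wise error and raises the chance of establishing the full hypothesis by 14 to 18 points in three of the five scenarios examined. The gain is 5 points where power is already high and 8 points (6% to 14%) where NIPPV is assumed close to CPAP.

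These sizes rest on 252 analysed infants per arm and on NIPPV rates that the protocol does not set. For the same reason the chance of a split result can only be given as a range, about 7% to 90%. The validity of the step-down rule depends on there being exactly three arms, not on any assumed rate. This is an improvement worth making, not an error that would invalidate the trial.

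**What to change.** 1. In Statistical methods {20a}, for the primary outcome, replace the flat rule with a three-arm chi-square at two-sided 0.05, then each pair at two-sided 0.05 only if the global test is significant. Shaffer or Holm step-down on the three pairs is an acceptable alternative and never rejects less than Bonferroni. Name one procedure only.
2. Make the matching change in the missing-data section {20c}, which repeats P < 0.0167.
3. Leave 0.0167 in Sample size {14} as the conservative sizing basis.
4. In the same edit, confirm that the hypothesis in Objectives {7} is supported only if both NIPPV contrasts favour NIPPV, and that one significant contrast supports a conclusion about that pair alone.
5. Settle this before outcome data by arm are seen, and date it. It affects the evaluation of results, so the section on protocol amendments {25} calls for ethics notification and a registry update.

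**Cost.** No added infants or data, but a formal amendment during recruitment. Confidence intervals that are simultaneous over the three pairs will not match the step-down decisions exactly, and the report should say so.

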### Intervention description {11a}

Infants enrolled in the study will be randomly assigned to one of the three groups: the HFNC group, CPAP group, or NIPPV group. Once assigned to a specific group, the infants will immediately begin the corresponding intervention based on the assigned group.

Before applying the assigned intervention, each newborn will be assessed the severity of RD using the Silverman Andersen score (SAS) [31]. This approach ensures a standardized and systematic evaluation of RD severity before commencing the assigned intervention, allowing for a consistent baseline comparison across the different treatment groups. Then, the assigned NIV can be applied.

#### Ventilators

HFNC: HFNC will be provided by devices that deliver a blend of heated and humidified gas mixture of air and oxygen at gas flows exceeding 1 L/ min via binasal cannula, including but not limited to Drager VN300, Drager C500, Fabian, Mindray NB350.

CPAP: CPAP will be provided by devices with pressure that is measurable and controllable that transport heated and humidified gas via binasal nasal prongs or nasal masks, including but not limited to Drager VN300, Drager C500, Fabian, Mindray NB350.

NIPPV: NIPPV will be provided by devices that able to provide sufficient pressure mentioned in the protocol (as indicated below), including but not limited to Drager VN300, Drager C500, Fabian, Mindray NB350. “NIPPV” in this trial is a broad term, a form of noninvasive respiratory support combining CPAP with intermittent higher pressure, including traditional NIPPV and Bi-level positive airway pressure (BiPAP) [35, 36]. When the pressure of BiPAP cannot meet the pressure required by the protocol, it can be replaced with other ventilators that can provide sufficient pressure.

#### Interface

In the CPAP group and the NIPPV group, neonates will be provided with soft, short binasal nasal prongs or nasal masks that are specifically matched with the ventilator being used. The size of nasal prongs will be chosen based on the diameter of the nares, ensuring the largest size that fits comfortably without compressing the surrounding tissues, in accordance with the manufacturer’s recommendations. Similarly, the size of the nasal masks will be selected according to the manufacturer’s guidelines to ensure an appropriate fit and effective respiratory support. To minimize the risk of nasal trauma, nasal prongs and masks can be used alternately, depending on the clinical situation.

For the HFNC group, neonates will use binasal cannulas with a diameter smaller than 50% of the nares’ size. This selection aims to reduce the risk of excessive air pressure and ensures safe and effective delivery of the heated and humidified gas provided by the HFNC system [37].

